### Planned statistical analysis

Research Electronic Data Capture (REDCap) [41] will be used for recruitment and data management in this study. The primary analysis will be an intention-to-treat analysis in which all subjects are retained in the group to which they were allocated and included in the analysis, irrespective of their compliance with allocated treatment. Statistical analysis in this population is used to determine statistical significance. The per-protocol population with inclusion of all patients without major protocol violations will be also analyzed. For confirmatory analysis, the primary endpoint will be assessed using the Mann-Whitney *U-*test. For secondary endpoints, categorical variables will be assessed using Chi-square tests or Fisher’s exact test, while continuous variables will be assessed using Student’s *t*-test and the Wilcoxon rank sum test, where appropriate. With regard to the exploratory analysis, adjustments will not be made for multiple comparisons. Multivariate analysis will be performed to define positive and negative predictors of specific primary and secondary outcomes. Last-observation-carried-forward method will be used to impute missing data. Statistical significance will be declared if the two-tailed *P*-value will be less than 0.05. Two-sided 95% confidence intervals will be calculated for continuous variables. All statistical analyses will be performed with SPSS (SPSS Inc., Chicago, IL, USA) and SAS (SAS Institute, Inc., Cary, NC, USA) software.

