## Background

Stroke still constitutes a leading cause of death and ranks number one among all causes of serious long-term adult disability in Europe and the United States [1,2], underscoring the need for adjuvant acute and preventive stroke therapies that reduce both the devastating human and economic burden of this disease.

More than two-thirds of acute ischemic stroke (AIS) patients suffer from sleep apnea of variable degree compared to 5 to 15% in the general population [3-6]. Moreover, in a prospective cohort study, patients with moderate to severe obstructive sleep apnea (OSA) had an almost two-fold increased risk for stroke and death after adjustment for other traditional vascular risk factors, thus establishing OSA as an independent risk factor [7,8]. Following stroke, sleep apnea negatively affects the length of hospitalization and short-term as well as long-term outcomes, likely through its association with an increased risk of neurological deterioration during acute and subacute phases of stroke [4,9-12]. Neurological deterioration during the early phase of AIS can occur between one and two out of five patients and it is independently predicted by sleep apnea and associated with unfavorable outcome [9,13].

Numerous studies including serial transcranial Doppler (TCD) in patients with AIS provided evidence that persisting large-artery steno-occlusive disease and corresponding collateral failure, leading to depletion of oxygen and nutrients to penumbral tissues, appear to be the most relevant pathogenic mechanisms for neurological deterioration [14-17]. Thus, it seems intuitive that further hemodynamic and perfusion derangements may do harm by facilitating hypoperfusion and ultimately lead to expansion of infarction to penumbral areas (or even oligemic tissues surrounding the ischemic penumbra) with neurological deterioration as the clinical correlate [18].

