### Study procedures

Study physicians will obtain baseline NIHSS scores, determine patient eligibility and obtain informed written consent from each patient prior to any study-related procedures. Patients allocated to the active group will receive non-invasive ventilatory treatment with auto-BPAP (Philips Respironics, Auto-BIPAP Biflex®, Herrsching, Germany) within 24 hours of symptom onset, and for a maximum of 48 hours during diurnal and nocturnal sleep or somnolence, from the beginning of study randomization (Figure 1). This approach warrants that all patients in the active group will receive an intention-to-treat all potential apneic episodes independently of their sleep cycle and somnolence. During the study period, oral and tube feeding intake will be allowed according to local institutional protocols. The auto-BPAP device automatically adjusts expiratory (EPAP) and inspiratory positive airway pressure (IPAP) levels to meet patients’ needs and will be configured to pressure settings that are identical in all patients in the active group: possible minimum EPAP 4 mbar; possible maximum IPAP 25 mbar; maximum difference between EPAP and IPAP (delta) 8 mbar; Biflex 2. The device records sleep-related respiratory events as well as duration of its use. Attachment of the device and initiation of treatment is performed by the study personnel who will receive training specific to the device by a sleep neurologist experienced with the study device.

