### Primary endpoint

Early neurological recovery will be assessed as any improvement on the NIHSS score at 72 ± 12 hours from randomization. Physicians or qualified study personnel, other than those involved in acute treatment (that is, blinded to randomization) and who are certified in performing NIHSS scoring, will obtain the NIHSS scores.

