### Secondary endpoints

Tolerability will be assessed by patient adherence to auto-BPAP (defined as tolerating the treatment during sleep or somnolence for at least four hours continuously).

*Safety* will be assessed by:

(i) frequency of serious adverse events (that is, aspiration, aspiration pneumonia defined as combined radiologic, white blood count and clinical findings, respiratory failure with/without intubation) during treatment period that in the opinion of the study physician are causatively and timely (for a maximum of 72 hours from treatment initiation) related to auto-BPAP. For comparison, patients in the control group will be monitored for respiratory complications within 72 hours from randomization. All deaths in both groups during hospital stay;

(ii) frequency of all complaints and possible side effects of auto-BPAP (that is, local irritation of skin/mucosa, mucosal dryness, nausea/vomiting);

(iii) any concerns by hospital nursing staff will be documented as adverse events since patients will be under standard of care repeated assessments set by admission protocols and treating physicians.

Signal-of-efficacy:

Clinical and functional outcomes will be assessed by:

(i) frequency of neurological deterioration (increase in baseline NIHSS score ≥ 4 points) at 24, 48 and after 72 hours from randomization by blinded observers;

(ii) frequency of early neurological improvement (decrease in baseline NIHSS score ≥ 4 points) at 24, 48 and after 72 hours from randomization by blinded observers;

(iii) good functional outcome (mRS score 0 to 2) at discharge and at three months by blinded observers, and ordinal analysis of the mRS at three months;

(iv) all deaths and any TIA or new ischemic stroke during hospitalization or within three months of protocol initiation.

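### Carrying the last score forward gives patients who die or become unscorable before 72 hours an earlier NIHSS, which can bias the NIHSS comparisons if such losses differ between arms

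*Protocol article*

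**What the plan says.** Under Planned statistical analysis, the protocol article gives one rule for missing data and no exception: "Last-observation-carried-forward method will be used to impute missing data". The same section makes the primary analysis intention-to-treat, so that "all subjects are retained in the group to which they were allocated and included in the analysis". The confirmatory test is Mann-Whitney.

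The primary endpoint is "any improvement on the NIHSS score at 72 ± 12 hours from randomization". Among the secondary endpoints is the "frequency of neurological deterioration (increase in baseline NIHSS score ≥ 4 points) at 24, 48 and after 72 hours from randomization". The scores available to carry forward are therefore the baseline score taken before randomisation (Study procedures) and those at 24 and 48 hours.

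The article gives no NIHSS value or rank to a patient who has died, or who is intubated, sedated or otherwise unscorable at 72 hours. Death and respiratory harm do have their own places under Secondary endpoints: "all deaths and any TIA or new ischemic stroke during hospitalization or within three months of protocol initiation", in-hospital deaths under safety, and aspiration, pneumonia and "respiratory failure with/without intubation" within 72 hours in both arms.

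**The concern.** In the first 72 hours of a stroke with arterial obstruction, a missing NIHSS may well mean that the patient got worse. The last score then comes from before the event:

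- If it is the baseline score, the patient enters as unchanged.
- If it is a 24- or 48-hour score better than baseline, the patient enters as improved.
- If it is already somewhat worse, the patient enters with that milder worsening.

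The deterioration endpoint goes the same way unless the last score had already risen by 4 points.

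Whether this biases the comparison depends on which arm loses more patients and why. Respiratory failure is among the harms that the plan itself monitors, so a loss rate that differs by arm is possible. The Discussion says the results will be used to power a phase III trial, so a distorted NIHSS effect would carry into that design.

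**Working it through.** **The plan's own figure.** 48 patients with a 20% allowance for missing data and tolerability problems: 48 / (1 − 0.20) = 60, or 30 per arm. This reproduces. The allowance is 0.20 × 30 = 6 patients per arm. It is not a rate of death or unscorability, and the article gives none.

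**Primary comparison.** Let θ be the probability that an auto-BPAP patient improves more than a control, plus half the probability of a tie. This is what the Mann-Whitney test addresses. Let p_A and p_C be the shares lost through death or unscorability. Let q be the probability that a carried score beats the change in a scored patient, counting ties as half. With no effect among scored patients and the same distribution of carried scores in both arms:

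θ = 0.5 − (p_A − p_C)(0.5 − q)

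Worst rank is q = 0. The share of the disadvantage hidden by carrying forward is therefore q / 0.5 = 2q, whatever the loss rates.

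Assumed inputs:

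- p_A = 0.15 and p_C = 0.05.
- Change in scored patients: normal with mean 1.4 (the control mean under Sample size), rounded to whole points.
- SD 1.34. The article states none. This value follows from a 0.9-point difference with P = 0.022 if the source study analysed 25 per arm: 0.9 / (2.367 × √(2/25)) = 1.34.

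Worst rank gives θ = 0.5 − 0.10 × 0.5 = 0.450.

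| Carried score (improvement) | q | θ under carry-forward | Share hidden |
|---|---|---|---|
| Mean 0.5, SD 1 | 0.306 | 0.5 − 0.10 × 0.194 = 0.481 | 61% |
| Baseline (0) | 0.165 | 0.5 − 0.10 × 0.335 = 0.466 | 33% |
| Already worse: mean −2, SD 2 | 0.085 | 0.5 − 0.10 × 0.415 = 0.459 | 17% |

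For the baseline row, q is P(change < 0) + ½P(change = 0) = 0.078 + 0.086. Simulated trials with 30 per arm agree with the table to within about 0.002. With SD 1.09, the value that 24 per group at 80% power implies, the shares are 57%, 24% and 15%.

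**Smaller or balanced losses.**

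- With 2 of 30 versus 1 of 30 (6.7% vs 3.3%) and the first carried score: 0.5 − 0.033 × 0.194 = 0.494, against 0.5 − 0.033 × 0.5 = 0.483 with worst rank. The gap is about 0.01.
- With p_A = p_C, both methods give 0.500.
- If the control arm loses more, the sign reverses and the rule works against auto-BPAP.

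**Effect on the test.** In simulations with 3,000 runs, SD 1.089, no effect among scored patients and losses of 15% vs 5%, the test rejected in 4.8% of trials with a partly improved carried score, 8.1% with baseline carried and 10.5% with worst rank. Nearly all the rejections under baseline and worst rank went against auto-BPAP. Those in its favour were 1.1%, 0.7% and 0.5%.

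**Deterioration endpoint.** Each truly deteriorated patient whose last score did not yet show it removes 1/30 = 3.3 percentage points from the arm's rate. A true 20% (6 of 30) is recorded as 5/30 = 17%, 4/30 = 13% or 3/30 = 10% with one, two or three such patients.

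**The case against.** The strongest reply is that the affected patients may be few. A perceived malignant course and a perceived need for intubation are exclusions, and the DSMB section expects serious adverse events in fewer than one in ten patients, not all of which would prevent scoring. The Background statement that "Neurological deterioration during the early phase of AIS can occur between one and two out of five patients" concerns worsening, and a patient who has worsened can still be scored. All of this stands. It limits the likely size but does not make the rule right for those it reaches.

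Several stronger readings are tempting, and the documents do not support them:

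- A reader might infer that the rule hides the trial's main outcome. The primary endpoint is improvement. Deterioration is secondary, and worsening scored at 24 or 48 hours is already captured.
- A reader might infer that harm disappears. Deaths and respiratory events are separate endpoints, and a DSMB with a halting rule sees serious adverse events. Nor did carrying forward produce false efficacy in the simulated scenario: rejections favouring auto-BPAP stayed below 2.5%.
- A reader might take 60% as the share hidden. That needs a carried score that was improving in patients about to die or be intubated.
- A reader might say that three such patients understate deterioration by 10 points. That is an upper bound. It requires all three to have risen by 4 points and none to have shown it at the last score.
- A reader might fear that a discharge mRS replaces a later death. A known death is an observed outcome, and deaths to three months are counted.

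The article also does not say outright that death counts as missing. This follows from an unrestricted rule combined with an all-patients analysis, and an analysis plan that is not shown may add a death rule. What the article itself fixes is still the carry-forward. Finally, for patients missing for neutral reasons while recovering, the carried score is worse than the true one, so the bias has no fixed direction.

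**Conclusion.** The point holds in a limited form. Read literally, the stated rule scores patients who died or became unscorable before 72 hours as if their last earlier state had persisted. This reaches the primary NIHSS comparison and the binary NIHSS endpoints, and nothing else.

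At assumed losses of 15% vs 5%, θ is 0.46 to 0.48 instead of 0.45, so roughly 20% to 60% of the disadvantage is hidden (17% to 61% by the exact calculation). At 6.7% vs 3.3% it is about 0.49 instead of 0.48. With equal losses there is no bias. Each affected patient lowers an arm's recorded deterioration rate by at most 3.3 percentage points.

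The loss rates, the carried scores and the SD are all assumptions. The effect is small with one or two events, and it becomes material only if condition-related losses are frequent and differ between arms.

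**What to change.** Before unblinding, replace the single sentence on missing data with these rules:

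1. In the Mann-Whitney test, rank patients who die, or who cannot be scored because of their condition, before the 72-hour assessment below all scored patients.
2. In the binary NIHSS endpoints, count them as not improved and as deteriorated.
3. For other missing 72-hour scores, use multiple imputation by arm from the baseline, 24-hour and 48-hour NIHSS.
4. State that death is mRS 6 and is never imputed.
5. Keep last observation carried forward as a sensitivity analysis.

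The cost is wording and modest programming, on scores already scheduled. Worst rank also makes the endpoint partly a composite of death and unscorability, and it loses power when such events are frequent in both arms. In the simulation of the 0.9-point effect (SD 1.089), power with 5% lost in each arm was 74%, against 78% to 81% under carry-forward. With 20% lost in each arm it was 44%, against 54% to 72%.

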## Discussion

We expect that this study will advance our understanding of how early treatment with non-invasive ventilatory treatment can counterbalance, or possibly reverse, the deleterious effects of sleep apnea in the acute phase of ischemic stroke. Our assumptions for sample size were based on a relatively small effect size as even slight improvements on the NIHSS score appear to be a strong predictor of good functional outcome after stroke [42]. The study will provide preliminary data to power a phase III study of auto-BPAP in the acute phase of cerebral ischemia.

## Trial status

At the time of manuscript submission, recruitment of study patients is ongoing. Initial recruitment was started in May 2013.

## Abbreviations

AIS: Acute ischemic stroke; BPAP: Bilevel positive airway pressure; CPAP: Continuous positive airway pressure; CTA: Computed tomography angiography; DSMB: Data safety monitoring board; EPAP: Expiratory positive airway pressure; IPAP: Inspiratory positive airway pressure; MRA: Magnetic resonance angiography; mRS: Modified Rankin scale; NCT: National clinical trial; NIHSS: National Institutes of Health Stroke Scale; OSA: Obstructive sleep apnea; REDCap: Research electronic data capture; SAE: Serious adverse events; TCD: Transcranial doppler.
